### Medication

In both trials the medication provided is prednisolone. Prednisolone will be allocated based on two bodyweight classes. The low weight class (patients below 50 kg), will receive prednisolone treatment based on a body weight of 45 kg. The high weight class (patients 50 kg and more) receives treatment based on a body weight of 60 kg.

#### Treatment arms

In the Clinical trial patients in the treatment arm receive prednisolone for 32 weeks, in tablets of 5 mg. The control arm will follow a regimen of 20 weeks and receive placebo tablets to keep the number of tablets equal to the treatment group for effective treatment time and duration. The dose in both intervention and control arm starts at 1 mg/kg/day (either 45 or 60 mg/day depending on weight class) and will be tapered down over 32 and 20 weeks, respectively. Figure 1a shows the dose over time of both arms in the Clinical trial. In contrast to previous trials, the middle range of the prednisolone dose will be maintained at a high level (0.44 mg/kg/day) for a longer period (12 weeks). In the Subclinical trial patients receive either prednisolone or placebo for 20 weeks in tablets of 5 mg. The prednisolone dose starts at 1 mg/kg/day (either 45 or 60 mg/day depending on weight class) and will be tapered down over 20 weeks. Figure 1b shows the timeline and dosage. The total dosage of prednisolone over 20 weeks will be 2.8 grams for patients under 50 kg body weight, and 3.7 grams for patients over 50 kg body weight.

**Figure 1 F1:**
[figure not shown]
**a. Timeline prednisolone dose for patients under 50 kg in the Clinical trial . b**. Timeline prednisolone dose for patients under 50 kg in the Subclinical trial.

#### Adverse events

Prednisolone has known adverse events, ranging from mild adverse events, such as moon face, fungal infections and acne, to serious adverse events such as peptic ulcer, osteoporosis glaucoma, cataract, psychosis, diabetes and hypertension [18,19]. Serious adverse events have not been encountered frequently in previous trials studying prednisolone for treating NFI in leprosy patients [20], however strict monitoring of adverse events will take place in the TENLEP trials. In case of serious adverse effects the PI will break the key and initiate an individualized treatment scheme. In the event of minor side effects additional medication will be prescribed according to normal protocol in the clinic, but the key will not be broken.

### Data collection

#### General assessments

Before intake, the general health of all possible eligible patients will be checked and history will be taken according to the protocol. Additionally, patients will be tested for specific medical conditions related to neuropathy and prednisolone intake such as diabetes mellitus (urine test) and osteoporosis (FRAX). Leprosy status will be categorized using both WHO classification (PB/MB), and Ridley-Jopling classification [21]. The latter will be done on clinical grounds, but a skin biopsy can be taken on voluntary basis for confirmation of the classification by a trained pathologist. For this procedure an additional consent procedure is in place. Of each patient a slit skin smear will be taken for determining the Bacteriological Index (BI).

#### Clinical nerve function tests

After intake, eligible subjects will be assessed for clinical sensory and motor nerve impairment. The clinical sensory function is tested with monofilaments using a standard set of 5 Semmes-Weinstein monofilaments ranging from blue (200 mg) to pink (300 g) [22]. This test of touch sensibility is based on indenting the skin surface with a series of standard nylon filaments. For each thickness it is recorded whether or not the patient feels the touch, starting with the thinnest filament. For hands the normal threshold is the blue filament and for feet the purple (2 mg) filament; when these filaments are felt by the patient it results in a score of 0. The score increases with 1 for each thicker filament not felt, with a maximum score of 5 in hands and 4 in feet (filament of 300 g not felt) for every site. Each nerve will be tested on 3 sites. The trigeminal nerve is tested by assessing the blink regularity. A patient is diagnosed as having sensory impairment if the monofilament threshold is increased by three or more monofilament levels in one single nerve (over 3 sites).

Motor nerve impairment will be assessed with Voluntary Muscle Testing (VMT) using the 0–5 MRC scale [23,24]. The test is performed by checking the ability of the patient to move a body part to a given position and to hold that position against resistance applied by the tester. A nerve scoring lower than 5 is considered impaired. When a single score of 4 is found this score should be independently confirmed by a second assessor.

#### Subclinical nerve function tests

When new patients show no abnormal values by VMT and MFT they will be tested further for possible inclusion in the Subclinical trial. For detecting subclinical neuropathy sensory and motor Nerve Conduction Studies (NCS), carried out with the Neurocare 2000® EMG machine (BioTech Ltd, Mumbai), and Warm Detection Threshold (WDT) test, using the TSA II (MEDOC, Israel), will be performed. NCS and WDT will take place in an air-conditioned room at approximately 20-25°C.

All assessments will be carried out at both sides of the body. Table 1 shows which nerves will be tested and methods used. MFT and VMT will be assessed at start of the trial and subsequently every month in both studies and follow-up periods on all subjects. WDT, Sensory Nerve Conduction (SNC) and Motor Nerve Conduction (MNC) will be carried out at baseline, end of treatment period (20 weeks) and at 12 and 18 months. For the Clinical trial additional information will be obtained using the Reaction Severity Scale (RSS) [25], the Screening of Activity Limitation and Safety Awareness (SALSA) scale [26] and the Participation Scale [27]. All scales will be filled in at baseline, end of treatment period (32 weeks), 12 and 18 months.

**Table 1 T1:** Nerves assessed by the different methods

**Nerve**	**VMT**	**MFT**	**MNC**	**SNC**	**WDT**
Trigeminal		blink			
Facial	x				
Ulnar	x	x	x	x	x
Median	x	x	x	x	x
Radial	x	x		x	x
Common peroneal	x		x		
Post. Tibial	x	x	x		x
Sural		x		x	x

#### Reliability and normative studies

Prior to intake inter-tester reliability studies have taken place for all assessments (MFT, VMT, WDT, NCS) to test and improve comparability of the results and ensure high measurement quality. After reliability studies for NCS and WDT, normative studies were carried out to establish the local normal values for each separate collaborative centre. For each nerve a minimum of 150 normal subjects from surrounding areas were tested, equally spread over both sexes and 3 age categories (15–30, 31–45 and 46–60 years of age). Normal subjects will be screened to ascertain they do not have diabetes or nerve function impairment.

#### Standard operating procedures and training

For all assessments standard operating procedures (SOP) have been developed. To achieve consistency of the assessments between all research centers, the PI and two main assessors of each centre received training in research protocol procedures and handling equipment. In addition, an online Good Clinical Practice (GCP) course was completed by all PI’s.

### Outcome measures

#### The Clinical trial

The primary study outcome is the proportion of patients with restored and improved nerve function (of all nerves) measured by VMT/MFT at 18 months. Secondary outcomes are based on results of the Reaction Severity Scale, SALSA and Participation Scale (Figure 2). Furthermore, a Count of Nerve Function Impairment (CNFI) will be computed to measure the results of treatment on nerve function, with special interest for most commonly affected nerves. The CNFI will consist of the count of nerve function impairments detected by monofilament and VMT testing and will be validated in this trial.

**Figure 2 F2:**
[figure not shown]
Overview of intake, assessments and outcomes in the Clinical and Subclinical trial.

#### The Subclinical trial

The proportion of patients developing clinical NFI as measured by MFT and VMT is the primary outcome indicator (Figure 2). Secondary outcome measures focus on results of the specific assessments for detection of subclinical neuropathy (WDT, SNC and MNC).

### Data analysis

After the data is entered for each centre, data will be checked and cleaned. Regular weekly back-ups will be made for local off-site storage in addition to a monthly upload of data via a web-based repository to the project statistician.

#### Reliability studies

Inter-rater reliability for categorical outcomes of VMT and MFT are assessed using weighted Kappa statistics. Comparing differences and averages of paired assessments for WDT, SNC and MNC tests are based on Bland-Altman plots. In addition, a mixed model analysis of variance will be used to compute the intraclass correlation coefficient.

#### Normative studies

To determine normative values for WDT and NCS for each centre, outliers are excluded before limits of normal function are calculated using an approach based on regression analysis taking into account age-related trends. The 97.5^th^ percentile is used to define abnormal function.

#### Primary outcomes

Analysis of primary outcomes will be done at 20 (Subclinical trial) or 32 weeks (Clinical trial), 12 and 18 months. Possible effects of potential covariates (gender, age, leprosy classification) will be assessed with ANCOVA. All analyses will be carried out using Stata statistical software.

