#### Sample size calculation

For the Clinical trial a recovery of 60% is presumed for the standard regimen in the control group [17]. To detect a recovery of 70% in the treatment group, compensating for 20% of loss to follow-up, a total of 720 subjects need to be enrolled.

The INFIR study shows that of the leprosy patients having subclinical neuropathy 16% will eventually develop clinical NFI [1]. For the Subclinical trial we assume a reduction in patients developing clinical NFI by half in the treated group (8%). Anticipating a loss to follow-up of 20% at 18 months, a sample size of 275 subjects per trial arm is required. For both sample size calculations a one-tailed alternative hypothesis, 80% power and 5% significance is used.

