This study will be the first to evaluate prednisolone treatment for the prevention of clinical NFI in people affected by leprosy diagnosed with subclinical neuropathy. The results of the preceding TRIPOD trial provide some insight in possible effects of prednisolone in preventing new NFI [28]. To prevent new NFI and reactions, leprosy patients with and without pre-existing NFI at diagnosis (as determined with VMT and MFT) received a prophylactic low dose of prednisolone (20 mg/day) for four months, tapered down in the last month. Although a reduced incidence of new NFI and reactions was observed at the end of treatment at four months, this was not sustained at one year. More important however, the preventive effect of prednisolone at four months was more than three times higher in patients with no pre-existing NFI [28]. A second study that has some similarities with our Subclinical trial is of that of Capadia et al. [29], who studied the effect of prednisolone on neuropathy as assessed with NCS. In their study, neuropathy was divided in mild, moderate and severe groups, as percentages deviating from normative values. Their findings suggest that a 12-week prednisolone course is not effective in preventing or reversing nerve damage. However, they found that mildly affected nerves showed higher improvement rates than moderately and severely affected nerves (53%, 21% and 14% of the nerves improved respectively).

The better outcomes of prednisolone treatment and prophylaxis on non-affected and mildly affected nerves from both studies of TRIPOD and Capadia et al. [29] show the importance of early treatment of neuropathy in leprosy patients. With the Subclinical trial we hope to establish that prednisolone treatment can prevent the development of clinical NFI and in this way can prevent disabilities and deformities in newly diagnosed leprosy patients.

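### The Subclinical trial's primary outcome has no decision time, yet it is analysed as primary at 20 weeks, 12 and 18 months without ranking

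*Protocol article*

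**What the plan says.** Four places in the protocol article bear on this.

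- **Outcome measures, The Subclinical trial:** "The proportion of patients developing clinical NFI as measured by MFT and VMT is the primary outcome indicator". No time is attached. The abstract's description of this outcome gives none either.
- **Outcome measures, The Clinical trial:** the primary outcome is "measured by VMT/MFT at 18 months". Here the time is explicit.
- **Data analysis, Primary outcomes:** "Analysis of primary outcomes will be done at 20 (Subclinical trial) or 32 weeks (Clinical trial), 12 and 18 months". All three times stand under the primary heading, and none is called main or supportive.
- **Sample size calculation:** "For both sample size calculations a one-tailed alternative hypothesis, 80% power and 5% significance is used". The Subclinical trial is sized for 16% against 8%, with 20% loss to follow-up at 18 months, giving 275 per arm. The section on follow-up sets 18 months for both trials.

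The Discussion also describes an earlier trial of prophylactic prednisolone. It saw a reduced incidence of new NFI and reactions at four months, when treatment ended, but "this was not sustained at one year".

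**The concern.** A primary outcome needs one time at which the trial is judged. Without it, the people reporting the Subclinical trial hold three results under one primary heading and no written reason to prefer any of them.

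The three times also answer different questions. At 20 weeks the active arm is just finishing prednisolone while the other arm has had placebo, so the comparison shows whether NFI is held back during treatment. At 18 months it shows whether NFI is prevented over a period that runs well past treatment. The earlier trial cited in the Discussion shows that the two answers can differ. If they differ here, the Subclinical trial could be reported as positive on the 20-week result or negative on the 18-month result, and either report would be consistent with the article as written.

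There is an error-rate side as well. The sample size provides for one test per trial. Three chances to succeed, each at the full level, raise the chance of a false claim above the stated 5%.

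**Working it through.** **Step 1. Reproduce the plan's own figure, to see how many tests it assumes.**
Inputs from the section on sample size: 16% and 8%, one-sided 5% (z = 1.645), 80% power (z = 0.842), 20% loss.

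- Uncorrected size per arm: n = [1.645·√(2·0.12·0.88) + 0.842·√(0.16·0.84 + 0.08·0.92)]² / 0.08² = 203.
- With continuity correction: (n/4)·[1 + √(1 + 4/(n·0.08))]² = 227.3, so 228.
- Adding 20%: 228 × 1.2 = 273.6, so 274 per arm against the stated 275.

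The same route for 60% against 70% gives 300 per arm, then 360, or 720 in total, exactly as stated. Both sizes follow from a single one-sided 5% test. Neither contains an allowance for repeated tests.

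**Step 2. Three tests with an any-time claim.**
Assumptions: each analysis uses the one-sided 5% level (the article states it only for sample size), significance at any time counts as success, and treatment has no effect.

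- Independent tests: 1 − 0.95³ = 14.3%.
- Correlated tests: 1 − P(Z₁, Z₂, Z₃ all below 1.645), with Z trivariate normal. The article gives no correlation, so a range is shown.

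| Equal correlation | Chance of at least one false positive |
|---|---|
| 0 | 14.3% |
| 0.4 | 12.5% |
| 0.5 | 11.8% |
| 0.7 | 10.3% |
| 0.8 | 9.3% |
| 0.9 | 8.0% |

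**Step 3. Narrow the range by reading the outcome as cumulative.**
If a patient who has developed NFI stays counted, the outcomes at two times are nested. With cumulative proportions p at the earlier time and q at the later, their correlation is √[p(1−q) / (q(1−p))]. For 6% and 12% this is √[0.06·0.88 / (0.12·0.94)] = 0.68. Only the final 16% comes from the article. The earlier proportions are assumed.

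| Cumulative NFI at 20 weeks, 12, 18 months | Correlations (20 wk–12 mo, 20 wk–18 mo, 12–18 mo) | Any-time false-positive rate |
|---|---|---|
| 9.6%, 13.6%, 16% (mostly early) | 0.82, 0.75, 0.91 | 8.8% |
| 8%, 12.8%, 16% | 0.77, 0.68, 0.88 | 9.4% |
| 6%, 12%, 16% | 0.68, 0.58, 0.85 | 10.0% |
| 4.1%, 10.7%, 16% (constant rate) | 0.60, 0.47, 0.79 | 10.7% |
| 1.6%, 8%, 16% (mostly late) | 0.43, 0.29, 0.68 | 11.8% |

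The last row is deliberately extreme. The others lie between about 9% and 11%.

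**Step 4. One decision time.**
With 18 months as the only deciding analysis, the rate is 5% one-sided. That is already the position in the Clinical trial if its outcome definition governs.

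**The case against.** The strongest reply is that 18 months is implied. Patients are followed for 18 months, the loss allowance in the Subclinical sample size is set at 18 months, and developing clinical NFI reads naturally as occurrence over the whole follow-up. The other analyses would then be a time course. This has weight, and it is why 18 months is the obvious time to name. It does not close the gap. The 16% in the sample size is described as what happens eventually, 18 months is attached only to loss, and the analysis section lists 20 weeks and 12 months as primary on equal terms. The Clinical outcome definition shows that the article states a time when it means to.

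A second reply is that multiplicity rules are commonly left to an analysis plan, which is not shown. That is fair, and the absence of an adjustment rule is not part of this point. The point is that the article itself lists three unranked primary analyses of an outcome with no time.

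A reader might infer more than the article supports:

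- **That the Clinical trial also lacks a decision time.** It does not: "The primary study outcome is the proportion of patients with restored and improved nerve function (of all nerves) measured by VMT/MFT at 18 months". If that sentence governs, its error rate stays at 5% one-sided, and the extra times can be read as supportive.
- **That the false-positive rate simply is 10%.** No rule that any time suffices is written, and the correlations are not given, so the figure is a conditional range.
- **That the one-tailed test causes the rise.** It is openly declared and sets the 5% starting point. The rise comes only from repeated chances.
- **That restored and improved function double the number of tests.** This rests on a plural in the abstract, whereas the Clinical outcome definition speaks of one primary outcome.

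**Conclusion.** The point holds for the Subclinical trial. Its primary outcome has no stated decision time and is scheduled for three unranked primary analyses. If success at any of them could support the claim, the one-sided false-positive rate is about 8% to 14% instead of 5%, and about 9% to 11% for plausible cumulative event timings. This rests on the any-time reading, on one-sided 5% at each analysis, and on assumed correlations or timings. The risk of opposite conclusions from the same trial depends on none of the correlation assumptions, and the article's own account of an earlier trial makes it a realistic one.

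For the Clinical trial this is only a matter of alignment. The outcome definition fixes 18 months, and the analysis section should follow it.

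**What to change.** 1. Under Outcome measures, The Subclinical trial, define the primary outcome as the proportion of patients developing clinical NFI cumulatively from randomisation to 18 months, as the single primary time. This agrees with the 18-month follow-up and with the 18-month loss allowance in the sample size.
2. Under Data analysis, Primary outcomes, state that the 18-month analysis decides each trial, and label the 20-week (Subclinical), 32-week (Clinical) and 12-month analyses as supportive.

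The change should be made before unblinding. It is wording only: visits, recruitment, treatment and sample size stay as they are. The downside is that an early benefit can no longer be claimed as the primary result. It can still be reported as a supportive finding.

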### Design of study

The TENLEP study consists of two multi-centre randomized triple blind controlled trials, both with two treatment arms, to study the effectiveness of prednisolone treatment restoring (Clinical trial) and in preventing (Subclinical trial) clinical nerve function loss.

Six institutions in four different countries participate in this study: Nepal (Lalgadh Hospital and Anandaban Hospital); India (JALMA Institute for Leprosy -Agra and Foundation for Medical Research-Mumbai); Bangladesh (Nilphamari Hospital); and Indonesia ([name] Surabaya). Anandaban Hospital and [name] will only take part in the Clinical trial. All collaborative institutions are referral hospitals specialized in the detection and treatment of leprosy. At each institution a Principal Investigator (PI) is responsible for the research at that centre. The overall responsibility lies with the International Coordinator (dr. [name]), guided by an International Steering Committee.

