#### Secondary outcomes

Continuous outcome measures will be analyzed with Analysis of (co)variance, assessing one or more covariates. Categorical outcomes may be analyzed using chi-squared test or log linear models. For Survival outcomes the log rank test will be used.

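### ANCOVA is the only method named for two yes/no primary outcomes; a binary-outcome model with centre and baseline impairment would suit them better, at a modest cost if left as it is

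*Protocol article*

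**What the plan says.** For the Clinical trial, Outcome measures states: "The primary study outcome is the proportion of patients with restored and improved nerve function (of all nerves) measured by VMT/MFT at 18 months". For the Subclinical trial it states: "The proportion of patients developing clinical NFI as measured by MFT and VMT is the primary outcome indicator". Each outcome is binary per patient.

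Data analysis, Primary outcomes, gives the analysis time points and the software, and then one method with a bracketed covariate list: "Possible effects of potential covariates (gender, age, leprosy classification) will be assessed with ANCOVA". No other model or test appears under that heading.

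The next subsection, Secondary outcomes, sorts methods by type of data. For continuous data: "Continuous outcome measures will be analyzed with Analysis of (co)variance, assessing one or more covariates". For categorical data: "Categorical outcomes may be analyzed using chi-squared test or log linear models".

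On design: "Six institutions in four different countries participate in this study". Two of the six take part only in the Clinical trial, so the Subclinical trial has four centres. For NCS and WDT, the normative studies were done to "establish the local normal values for each separate collaborative centre". The data collection section has MFT and VMT measured at the start of both trials, and WDT, sensory and motor conduction measured at baseline.

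**The concern.** By the article's own sorting, analysis of covariance belongs to continuous measures, yet it is what is named for two proportions. It models a yes/no result as a straight line with constant variance. Fitted risks can then fall below 0 or above 1, most easily at the low rates expected in the Subclinical trial (16% and 8%).

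The covariate list is also not the one the design suggests. Centre is in no stated model, although the hospitals are in four countries and set their own limits of normal for NCS and WDT. Baseline impairment is absent too. In the Clinical trial the outcome is recovery of the same nerve function whose loss at entry can range from mild to severe, so baseline severity is a natural prognostic factor. Leaving out strong prognostic factors gives away precision on data already in hand.

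**Working it through.** **Inputs.** From Sample size calculation: 60% versus 70% recovery (Clinical); 16% versus 8% developing NFI (Subclinical); 720 in total and 275 per arm; 20% loss; one-sided 5%; 80% power. Analysed numbers after 20% loss: 360 × 0.8 = 288 per arm (taking 1:1 allocation) and 275 × 0.8 = 220 per arm.

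**1. The plan's own figures.** The two-proportion formula with pooled null variance is n = [z₀.₉₅√(2p̄q̄) + z₀.₈₀√(p₁q₁ + p₂q₂)]² / (p₁ − p₂)².
- Clinical: [1.645√0.455 + 0.842√0.45]² / 0.01 gives 281 per arm, or 300 with continuity correction. Then 300 × 1.2 = 360 per arm, 720 in total, as stated.
- Subclinical: [1.645√0.2112 + 0.842√0.208]² / 0.0064 gives 203, or 228 with correction. Then 228 × 1.2 = 273.6, so 274 against the stated 275.

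The trials are thus sized on a comparison of two proportions, while the only model named is one for continuous data.

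**2. Does unequal variance spoil the ANCOVA test?** Subclinical variances are 0.16 × 0.84 = 0.1344 and 0.08 × 0.92 = 0.0736, a ratio of 1.83. Clinical variances are 0.24 and 0.21, a ratio of 1.14. With n per arm equal, the pooled standard error is √(2s²/n) with s² = (s₁² + s₀²)/2, which is √((s₁² + s₀²)/n), the same as the unequal-variance formula. For the Subclinical trial both are √(0.208/220) = 0.0308. The ratio of 1.83 therefore has almost no effect on the treatment comparison. Simulating the documented three-covariate model at 220 per arm gave a ratio of model-based to robust standard error of 1.000 and type I error of about 0.04 to 0.06.

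**3. Fitted risks outside 0 to 1.** For the documented covariates in the Subclinical trial, the simulated share was 0.3% to about 8%, depending on how prognostic they are assumed to be. A linear model that also held centre and baseline gave up to 5% (Clinical) and 14% (Subclinical).

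**4. Precision.** There were 1,500 simulated trials per setting, with 576 and 440 patients analysed. Assumptions that are not in the documents: equal centres, arms balanced within centre, the three listed covariates without prognostic effect, and centre SD and baseline-severity effect (log-odds per SD) both set to 0, 0.5 or 0.8.

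| One-sided power | 0 | 0.5 | 0.8 |
|---|---|---|---|
| Clinical, ANCOVA as documented | 0.816 | 0.818 | 0.814 |
| Clinical, logistic with centre and baseline | 0.819 | 0.843 | 0.872 |
| Subclinical, ANCOVA as documented | 0.847 | 0.815 | 0.816 |
| Subclinical, logistic with centre and baseline | 0.848 | 0.823 | 0.849 |

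The gains are 0.3, 2.5 and 5.8 points (Clinical) and 0.1, 0.8 and 3.3 points (Subclinical; 3.6 at most against a logistic model without centre and baseline). Nearly all of this comes from the added covariates and not from the link: a linear model with the same terms reached 0.867 (Clinical) and 0.845 (Subclinical) in the strongest setting. Type I error was 0.04 to 0.06 for every model.

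**5. Room for covariates.** Expected Subclinical events are 220 × 0.16 + 220 × 0.08 = 35.2 + 17.6, about 53. Arm, three centre terms, SNFS, classification, sex and age make 8 parameters, or 53/8 ≈ 6.6 events each. In the Clinical trial the smaller class is the non-recovered: 288 × 0.40 + 288 × 0.30 = 201.6. Ten parameters (five centre terms) leave about 20 each.

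**The case against.** The sentence on ANCOVA speaks of assessing possible covariate effects. It does not call ANCOVA the treatment comparison, and it can be read as a supporting analysis beside a plain comparison of proportions, which is how the trials were sized. That stands as a caution. But if ANCOVA is not the treatment comparison, the article names none for the primary outcomes, and ANCOVA remains the wrong scale for covariate effects on a proportion.

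The article condenses a fuller document, and a full covariate list is commonly left to an analysis plan that is not shown. The absence of centre and baseline impairment alone would therefore be no fault, and nothing in the article excludes them. The point rests on what the article does state: a model, and a list, that do not fit the outcome well. Centre and baseline come in as part of the better replacement.

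Fitted risks outside 0 to 1 matter little when the aim is to compare arms, and the power gain can be nil. Both are right, and they limit the size of the point.

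A reader might infer from the variance ratio of 1.83 that standard errors and intervals for treatment are wrong. With equal arms they are not, as step 2 shows. A reader might also infer that the wording lets covariates be picked after the results are seen. It is loose, but it names three covariates, and the documents do not show that more would be chosen later.

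**Conclusion.** The point holds in a limited form. The article names a method that its own scheme keeps for continuous measures, and applies it to two binary primary outcomes. The result would not be an invalid test. It would be a model on the wrong scale, with some implausible fitted risks, and a treatment estimate less precise than the recorded data allow.

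The loss is 0 to about 6 power points in the Clinical trial and 0 to about 4 in the Subclinical trial. Those ranges rest on assumed strengths of centre and baseline severity that the documents do not give, and the lower end is no loss at all. The case for baseline adjustment is strongest in the Clinical trial. In the Subclinical trial MFT and VMT are normal at entry by rule, so only the subclinical measures can serve. The change is worth making because it is cheap, not because the planned test would fail.

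**What to change.** Name one binary-outcome model as the treatment comparison for each trial, for example logistic regression, with all terms fixed before unblinding:
- **Clinical trial:** arm, centre, a baseline impairment measure built from MFT and VMT (such as the number of impaired nerves), leprosy classification, sex and age.
- **Subclinical trial:** arm, centre (four), baseline SNFS, classification, sex and age. With about 53 expected events, cut this list or use a penalised fit, and state which in advance.

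Report a standardised risk difference with its 95% confidence interval in both trials, so that the result is on the scale used for sizing. Keep analysis of (co)variance for the continuous secondary outcomes.

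The cost is a few lines of analysis-plan wording and different Stata commands. No new data are needed, since centre, MFT, VMT, NCS and WDT at baseline are already collected.
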